#### Interim analyses {21b}

There are no planned interim analyses for the trial or stopping guidelines. An internal pilot study will be conducted to check the initial assumptions about recruitment and feasibility of the trial. Data arising from the pilot phase will be reviewed by the Data Monitoring Committee (DMC) and Trial Steering Committee (TSC) who will recommend if any changes are required and if the trial should continue or not.

#### Qualitative sub-study analysis

Data will be analysed thematically following the conventions established by Braun and Clarke [32]. Interviews will be coded independently with a second-team member ensuring consistency and validity of the coding process. Data analysis will commence before data collection is completed, and coded interviews will be reviewed to inform on-going data collection strategies. Key ideas and themes which help to organise the data will be identified and modelled as part of this process.

The theory will be developed systematically using the constant comparison method [33] in order to maximise consistency and plausibility. Ideas and themes will be reviewed by the broader DISC team and DISC patient and public partners. Emergent theoretical categories and their properties will be contrasted with feedback received from the study’s stakeholders (e.g. principal investigators and members of the study’s patient and public involvement group).

Data from each treatment arm may be considered separately with distinct models for the two study treatments constructed along with a further model which considers Dupuytren’s symptoms and impact. These models will be considered alongside the clinical and economic data to inform the study findings and to inform recommendations for future clinical practice.

#### Photography sub-study analysis

Joint measurements obtained using participant taken photographs will be compared with goniometer readings and measurements obtained using clinician taken photographs, to assess whether there is reasonable agreement between these. Angles will be measured on photographs by observers, using anonymised digital images and a standardised measurement protocol.

Agreement between baseline goniometric measurements and measurements obtained using baseline participant photographs will be assessed for the MCP and PIP joints of the reference digit. The 95% limits of agreement, between the mean of the three repeated goniometric measurements obtained at baseline and the measurement obtained using the participant photograph, will be calculated for each joint following the methods of Bland and Altman [34]. The limits of agreement (and the 95% confidence intervals of these limits) for each joint (MCP and PIP) will be compared with a pre-specified magnitude of clinically acceptable disagreement of 10°.

Secondary analyses will look at the agreement between:
Goniometric measurements and measurements obtained using patient photographs at 3 and 6 months post-treatmentGoniometric measurements and measurements obtained using clinician photographs at baseline and 3 and 6 months post-treatment

Limits of agreement values and 95% confidence intervals will be reported for these comparisons by joint and where feasible by digit. Potential predictors of agreement (for both the primary and secondary comparisons) will be explored by regression analysis. Potential predictors include digit measured, contracture severity and image quality.

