Initial clinical effectiveness studies comparing collagenase with placebo [5] and a systematic review in 2015 [9] indicated that collagenase is better than placebo, particularly for contractures affecting the MCP joint [5]. Observational data on recurrence of Dupuytren’s contracture (a change in extension deficit of 6° between 3 and 6 months, or 20° from 3 months to 1 year post-treatment [6, 10]) suggest that it is higher following collagenase treatment than surgery 3 years after treatment.

Current evidence of the cost-effectiveness of collagenase and surgical correction is based on small retrospective studies [9] and so conclusions are limited.

Despite the existing available evidence, there is no robust randomised controlled trial evidence available on the clinical and cost-effectiveness of collagenase compared with limited fasciectomy surgery. There is also currently no robust evidence on the comparative recurrence rates of Dupuytren’s contracture following treatment with collagenase compared with limited fasciectomy surgery. A sufficiently powered randomised controlled trial is required to fill this evidence gap. Therefore, the UK National Institute for Health and Care Excellence (NICE) commissioned a full-scale RCT to provide a definitive answer on the effectiveness of these treatment options.

Overall, collagenase injections would have to not be inferior to limited fasciectomy surgery to permit recommendation for general use. The Dupuytren’s Interventions Surgery vs Collagenase (DISC) trial was designed as a pragmatic multi-centre, randomised controlled, non-inferiority, cost-effectiveness trial comparing injections of collagenase into the cord to surgical correction in the treatment of moderate Dupuytren’s contracture in adult patients.

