### Trial design {8}

The DISC trial is a two-arm, pragmatic, non-inferiority, randomised controlled trial investigating whether collagenase injection is not inferior to limited fasciectomy in the correction of Dupuytren’s contracture of the hand. The trial includes an economic evaluation, a qualitative sub-study, a photography sub-study and two nested studies within a trial of retention strategies.

**Table 1 Tab1:** DISC trial objectives

Objective	
1	To investigate whether collagenase injection is not inferior to limited fasciectomy in the *(impact of)* correction of Dupuytren’s contracture of the hand at 1 year^a^.
2	To investigate whether the *(impact of)* correction achieved after collagenase injection or surgical correction is maintained at 1 and 2 years^a^.
3	To investigate the cost-effectiveness of collagenase injections compared to limited fasciectomy at 1 and 2 years after treatment (from the NHS and Personal Social Services perspectives).
4	To investigate if the remote measurement of active extension and flexion using photographs is as good as goniometric measurements in a clinic to determine recurrence (photography sub-study).
5	To explore patient’s experiences and preferences of the different treatments (qualitative sub-study).

^a^*In terms of patient-reported hand pain and functionality as assessed by the PEM, as further detailed in the “Outcomes” section*

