##### Objective measures (recurrence, extension deficit and total active movement)

Recurrence (defined as a change in extension deficit of 6° between 3 and 6 months, or 20° from 3 months to 1 year after treatment [6, 10]), extension deficit and total active movement will be assessed using joint range measurements with a goniometer. A study-specific manual on how to perform joint measurements and use of goniometers which meet pre-specified criteria (permits measurement of up to 30° of hyperextension, measures flexion to 120°, measures in 2° increments) will ensure assessments are standardised.

Photographs of the participant’s reference hand (extension, flexion and AP views) will be taken in clinic. A study-specific manual will be used to standardise the images. If willing, participants will also take and return a photograph of their hand, again standardised using a study-specific procedure and video provided to participants

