##### Photography sub-study

To give the widest range of angles possible, we will recruit sufficient participants to provide 100 photograph sets before surgery and will also collect as many photograph sets as possible at 3 months, 6 months, 1 year, and 2 years post-treatment.

Participants who consent to participate in the photography sub-study will be shown how to take the required photographs of their hand at baseline and will be provided with detailed instructions. This will include a template to aid placement of the participant’s hand, an information leaflet on how to submit photos, and a link to a video showing how to take photographs. Documentation will be reviewed and approved by the patient and public involvement group prior to use in the study.

Sub-study participants will be asked to take standardised photographs of their study reference hand at baseline and all subsequent time points. Participants will receive a text message or letter at each time point to remind them to return photographs to the study team for this sub-study via email, SMS or post.

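### The photography sub-study is meant to judge recurrence, a change of 6° or 20°, but plans only single-visit agreement against a 10° margin tied to neither threshold and too loose for the 6° rule unless errors are strongly correlated between visits

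*Protocol article*

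**What the plan says.** Table 1 of the protocol article (Trial design {8}), objective 4, asks whether remote measurement of active extension and flexion "using photographs is as good as goniometric measurements in a clinic to determine recurrence".

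Under Objective measures, recurrence is "defined as a change in extension deficit of 6° between 3 and 6 months, or 20° from 3 months to 1 year after treatment". Background and rationale {6a} gives the same definition.

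Photography sub-study analysis sets the primary comparison: "Agreement between baseline goniometric measurements and measurements obtained using baseline participant photographs will be assessed". It covers both joint types, MCP and PIP, of the reference digit. The resulting 95% limits, with their confidence intervals, "will be compared with a pre-specified magnitude of clinically acceptable disagreement of 10" degrees. The secondary comparisons are participant photographs against goniometry at 3 and 6 months, and clinician photographs against goniometry at baseline, 3 and 6 months.

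Photography sub-study sets a target of 100 pre-surgery photograph sets, chosen to cover a wide range of angles, and then "as many photograph sets as possible at 3 months, 6 months, 1 year, and 2 years post-treatment". Table 2 schedules goniometry and photographs at 3 months, 6 months, 1 year and 2 years.

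**The concern.** The objective concerns a change within a person between two visits. The analysis concerns an angle at one visit. Agreement on a single pre-treatment angle does not show whether photographs pick up a later loss of correction.

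The margin is not connected to the definition it is meant to serve. Nothing in the article derives the 10° from the 6° or the 20° threshold. The two post-treatment visits at which agreement is examined, 3 and 6 months, are the endpoints of the 6° rule, where the margin is least suited. The 3-month-to-1-year rule has no listed comparison at its later visit, although both kinds of measurement are collected then.

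At stake is the conclusion of the sub-study. Limits inside 10° would naturally be taken as support for judging recurrence remotely, and the planned analysis would not have tested that use.

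**Working it through.** **Nothing to reproduce.** The 10° margin and the 100 sets are stated without derivation. The check is what a method that just meets the margin would do under the recurrence definition.

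**Inputs from the protocol article:** margin 10°; recurrence thresholds 6° and 20°; 100 baseline sets.

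**Assumptions:** normal errors; no bias; limits exactly at the margin; the same error SD at each visit; a rule counts as met when the change reaches the threshold. The correlation ρ of photo-minus-goniometer errors between visits is not given, so it is varied from 0 to 0.9.

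**Step 1, one reading.** SD of one difference = 10 / 1.96 = 5.10°. The share of single photo readings more than 6° from goniometry is 2 × [1 − Φ(6 / 5.10)] = 24%.

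**Step 2, a change between two visits.** SD of the discrepancy in change = 5.10 × √(2(1 − ρ)). At ρ = 0 this is 7.22°, so 95% of discrepancies lie within ±14.1°.

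**Step 3, the 6° rule.** False positive (zero goniometric change) = 1 − Φ(6 / SD). Missed (10° goniometric worsening) = Φ(−4 / SD).

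| ρ | SD of change discrepancy | 95% half-width | False positive at 6° | 10° worsening missed |
|---|---|---|---|---|
| 0 | 7.22° | 14.1° | 20.3% | 29.0% |
| 0.25 | 6.25° | 12.3° | 16.8% | 26.1% |
| 0.5 | 5.10° | 10.0° | 12.0% | 21.7% |
| 0.75 | 3.61° | 7.1° | 4.8% | 13.4% |
| 0.82 | 3.06° | 6.0° | 2.5% | 9.6% |
| 0.9 | 2.28° | 4.5° | 0.4% | 4.0% |

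**Step 4, correlation needed.** For 95% of change discrepancies to stay within 6°: ρ = 1 − (6 / 10)² / 2 = 0.82. Conversely, the single-reading limits needed are 6 / √(2(1 − ρ)): ±4.2° at ρ = 0, ±4.9° at 0.25, ±6.0° at 0.5 and ±8.5° at 0.75.

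**Step 5, stricter reading.** The article also sets the confidence intervals of the limits against 10°. If the outer confidence limit must lie at 10° with n = 100, then SD = 10 / [1.96 + 1.96 × √(1/100 + 1.96² / 198)] = 10 / 2.296 = 4.36°. False positives at 6° become 16.5% at ρ = 0, 8.4% at 0.5 and 2.6% at 0.75. The correlation needed falls to about 0.75.

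**Step 6, the 20° rule.** With SD 5.10°, the false-positive rate at ρ = 0 is 1 − Φ(20 / 7.22) = 0.3%, and lower for larger ρ. A 30° goniometric change is detected with probability Φ(10 / 7.22) = 92%, and higher for larger ρ. Single-reading limits of ±14.1° would already keep 95% of change discrepancies within 20° at ρ = 0. The 10° margin is tight enough here.

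**The case against.** **The baseline choice has a stated reason.** Pre-surgery sets are sought for the widest range of angles, which is ordinary practice in method comparison, and only baseline has a target number. Contracture severity is listed as a possible predictor of agreement, and 3- and 6-month limits will be reported, so a reader could set them against 6°. This stands as a reason to keep the baseline analysis. It does not make a single-angle comparison an answer about change.

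**Detail may sit in an unseen analysis plan.** That is possible. But the article itself fixes the primary comparison, the margin and the secondary visits, and it describes itself as the full protocol. The point concerns what is fixed there.

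**Stronger readings that a reader might infer, and that the document does not support:**

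- *Photographs meeting the margin could not detect recurrence.* The definition has two parts, and step 6 shows that the margin is adequate for the 20° part.
- *10 exceeds 6, so the margin is wrong on its face.* One is a tolerance for a single reading and the other a change between two. Stable within-patient error cancels in a change, so the comparison depends on ρ.
- *The plan would declare photographs adequate.* The article says only that the limits are compared with 10° and gives no pass/fail rule. Reading a clinically acceptable limit as the criterion is fair, but it is an inference.
- *A large share of patients would be misclassified.* The rates hold for a goniometric change of exactly 0° or 10°. The distribution of change is unknown, and goniometry carries error of its own, although objective 4 takes it as the reference.
- *All baseline joints are contracted by 30° or more.* Eligibility requires this in either joint, while agreement is assessed in both.
- *The main trial is affected.* Its recurrence outcome is measured by goniometer.

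**Conclusion.** The concern holds in this form: followed as written, the sub-study estimates single-visit agreement and does not answer objective 4. The 10° margin is linked to neither recurrence threshold. It is compatible with the 20° rule and too loose for the 6° rule unless errors are strongly correlated between visits (about 0.82, or 0.75 on the stricter reading), and no planned analysis estimates that correlation.

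The mismatch between objective and analysis rests on the text alone and is firm. The error rates are illustrations that depend on zero bias, limits at the boundary and the unknown correlation. If the observed limits turn out well inside 10°, the rates will be lower. The matter is confined to one sub-study objective, but it should be settled before that sub-study is analysed.

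**What to change.** Keep the baseline agreement analysis as planned. Base the conclusion for objective 4 on two added analyses against goniometry:

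1. Limits of agreement for the change in extension deficit, from 3 to 6 months and from 3 months to 1 year, compared with the 6° and 20° thresholds in the protocol's own definition.
2. Agreement on recurrence classification: sensitivity, specificity and kappa, with confidence intervals.

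Use the 1-year photographs for both. State that the 10° single-reading margin will not by itself support remote assessment of recurrence, and either justify it against the two thresholds or describe it as a margin for single angles only. If these analyses are not wanted, restate objective 4 as agreement on a single angle.

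No new measurements are needed, since photographs and goniometry are already scheduled at these visits. The cost is statistical. Later photograph sets have no target number, complete pairs will be fewer than at baseline, and recurrences may be few, so precision should be reported. The comparison with 6° is also stricter, and photographs may fail it.

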#### Studies with a trial (SWATs) analysis

Analyses of the retention thank you card SWAT will be conducted using logistic regression, adjusting for SWAT allocation, DISC trial allocation and relevant baseline covariates (if applicable). An unadjusted analysis will also be completed.

Analyses of the retention Christmas card SWAT will be undertaken centrally by the MRC funded PROMETHEUS team.

#### Plans to give access to the full protocol, participant level-data and statistical code {31c}

This document constitutes the full protocol. Following completion of the trial, datasets and statistical code used in this study will be available from the corresponding author on reasonable request.

#### Oversight and monitoring

##### Composition of the coordinating centre and trial steering committee {5d}

YTU will oversee and coordinate the management and running of the study. This will include trial management and coordination, statistical, economic and data management staff.

The trial management group (TMG) will meet quarterly and will consist of the Chief and co-investigators, members of YTU and the Academic Team of Musculoskeletal Surgery (AToMS) responsible for the study.

The Trial Steering Committee (TSC) will comprise two independent members (one clinician and one methodologist) and a patient and public representative. The TSC will provide overall supervision for the trial on behalf of the Sponsor and Funder.

##### Composition of the data monitoring committee, its role and reporting structure {21a}

A Data Monitoring and Ethics Committee (DMEC) will comprise three independent members (two clinicians, one statistician) and a patient and public representative. The DMC will be the only body to have access to unblinded comparative data during the trial should this be required. The DMC will monitor data and make any recommendations to the TSC on whether there are any ethical or safety reasons why the trial should not continue.

##### Adverse event reporting and harms {22}

Adverse events (AEs) related to the affected digit or hand, or to the study intervention or control will be recorded irrespective of whether they are expected or unexpected. AEs that may be expected are detailed in the Summary of Product Characteristics (for the intervention) [4] and in Table 3 for the control (See the “Outcomes” section). Any event which has a reasonable, suspected causal relationship to the study medication (intervention) will be deemed an adverse reaction.

Serious adverse events that are deemed related to the research and are unexpected will be reported to the Research Ethics Committee (REC) who approved the study. All AEs will be routinely reported to the TMG, TSC, DMEC and Sponsor. The DMEC will be responsible for reviewing related and unexpected serious adverse events.

Adverse events will be collected and reported through review of any complications associated with the intervention and control at each study visit and via spontaneous report should the participant report any adverse events between study visits. All AEs that are related to the study medication or procedures and which are unresolved at initial reporting will be followed up until resolution or the event is considered to be stable.

All adverse events will be reported in any associated, relevant publications arising from this trial.

##### Frequency and plans for auditing trial conduct {23}

The study will be conducted in accordance with the currently approved protocol, ICH Good Clinical Practice (GCP), relevant regulations, standard operating and trial-specific procedures.

Regular monitoring will be performed according to ICH GCP and the DISC Monitoring Plan. Data will be evaluated for protocol compliance and accuracy in relation to source documents. Following written standard operating and trial-specific procedures, the monitors will verify that the clinical trial is conducted and data are generated, documented and reported in compliance with the protocol, ICH GCP and the applicable regulatory requirements.

##### Plans for communicating important protocol amendments to relevant parties (e.g. trial participants, ethical committees) {25}

Important protocol modifications will be submitted to the REC and Health Research Authority (HRA) for approval having been agreed with the Funding Body, Sponsor, TSC, DMEC and the TMG. Minor modifications to the protocol will be agreed upon with the TMG and Sponsor before submission for approval to the REC and HRA. All amendments will be implemented in accordance with the guidance of the HRA. Trial participants will be written to, if necessary, to explain any changes.

##### Dissemination plans {31a}

Results from this study will be written up and submitted to peer-reviewed journals. A publications policy will be generated in advance to detail authorship, acknowledgements and review processes for any publications arising from the DISC Trial. Authorship will be determined in accordance with the International Committee of Medical Journal Editors.

## Discussion

The DISC trial has been designed to provide a robust answer to guide the treatment of Dupuytren’s contracture as regards the effectiveness of collagenase, in terms of patient-reported hand pain and functionality as assessed by the PEM. Overall, collagenase would have to not be inferior to limited fasciectomy surgery in order for it to be recommended for widespread use, and the DISC Trial will enable this comparison to be made. The study will assess rates of recurrence between the two treatments which is an important consideration for both patients and healthcare professionals when discussing available treatment options. Key also to patients, and the wider economy, is the return to function as soon as possible following treatment, which is also assessed within the DISC trial.

As noted, collagenase was withdrawn from the UK and European market for commercial reasons as of March 2020. The DISC trial team worked to secure sufficient stocks to continue recruitment to the contracted target. These efforts were driven by a clear steer by clinicians (site principal investigators and co-applicants) that results of this study continue to have an important bearing on treatment options offered to patients. These efforts were reviewed and supported by the funder (NIHR) and DISC trial oversight committees.

Collagenase continues to be produced and marketed in the USA for treatment of Dupuytren’s contracture. Therefore, this study would provide reliable information on which to base the reintroduction for clinical use in Europe. A similar study cannot be commissioned in the UK or Europe, given the current market withdrawal, making the DISC trial the only opportunity for a study in this region to collect reliable data in relation to the effectiveness of collagenase compared with limited fasciectomy. The results also provide a key component to a comprehensive assessment of treatment options for Dupuytren’s contracture. A plan of research for this is already underway with funding secured as part of the UK National Institute for Health Research-funded HAND2 trial [NIHR: 127393; ISRCTN: 18254597], which includes a package of work to bring together all treatment comparisons for Dupuytren’s contracture in an individual patient data network meta-analysis.

